#### Item about placebo appraisal of the Questionnaire on Responders’ Attitude Regarding Non-Specific Therapies^26^

At t2, participants rate the item about placebo appraisal online which encompasses the following three questions:

How would you define the term placebo?A rating of the positivity or negativity of the term.Do you believe that physical complaints can get better if you merely belief in the efficiency of a therapy?

#### Patient–provider connection items of the Healing Encounters and Attitudes Lists–German Short Version^27^

The Healing Encounters and Attitudes Lists - German Short Version (HEAL-S) provides an item bank to measure nonspecific factors in treatment. We collect the patient–provider connection item at t2 to control for the influence of provider perception.

#### Placebo intervention credibility is assessed online at t2 with the question

Did you believe that you received placebo pills during the study, that is, pills without any pharmacological content? The three answer options are:

Yes, I was sure that I received placebo pills.I had doubts that I received placebo pills.No, I did not believe that I received placebo pills.

Moreover, the OLP− group is asked whether they felt something was missing, whereas the OLP+ group is asked whether they found the provided rationale convincing and how it may have helped or confused them personally.

### Tertiary outcomes measures

Other, tertiary outcomes of interest are:

Sociodemographic variables: age, family and relationship status, sexual orientation, citizenship, country of birth, mother tongue, educational degree, employment status, height, weight and number of births and aborts, if participant has a GP/gynaecologist.Retrospective PMS Questionnaire sum score.Mini-International Neuropsychiatric Interview.Pregnancy test.Medical and gynaecological history.Concomitant pharmacological or non-pharmacological interventions and changes in all groups.Qualitative answers regarding treatment and study experience.Occurrence of side-effects/adverse events.Number of participants who withdraw from study participation.Number of participants from the TAU group who attend an OLP intervention after study conclusion.Number of participants from the intervention groups who show interest to continue the OLP intervention after study conclusion.Suicidality.

### Adverse events and safety monitoring

Study participants will be asked about any side-effects, including also treatment-emergent adverse-events or serious adverse events at t1 and t2. Suicidality, which is specifically associated with premenstrual dysphoric disorders,^28^ and generally found to be higher in the luteal (=premenstrual) phase,^29^ will also be assessed at each study visit and if necessary, safety actions will be provided.

## Sample size and statistical analysis of data

### Data management

For data management, Microsoft Excel and LabKey, which is hosted by the University of Basel, is used. Study data are collected at the web server-based software LimeSurvey. Only authorised study team members are able to view and export data. Entries and actions are marked with the initials of the respective study member.

### Sample size

A calculation with a power analysis on the basis of an F-test and an analysis of covariance for three groups, using the statistical software G*Power, indicated a total sample size of 206 participants needed for a power of 0.9 and a total sample size of 158 participants for a power of 0.8 to detect a medium effect size of f=0.25 (equals d=0.5) with an alpha-level of 0.05.

Since we will adopt a multilevel approach which enables more precise estimations, we also conducted a power analysis on a repeated-measures analysis of variance, using G*Power, whereby we are interested in the interaction between time (menstrual cycles, 3 levels) and study groups (3 levels). If the correlation for the outcome among the different time points (1–3 cycles) is assumed to be 0.5, then based on an alpha-level of 0.05, a power of 0.8 and a medium effect size of f=0.25, the required samples size is 36 (12 per group). Accordingly, for the main effect of menstrual cycle, we would need 30 participants (10 per group), and for the main effect of study group we would need 108 participants (36 per group). On this basis, we chose a conservative total sample size of 150 participants (50 per group). It is worth noting that most OLP studies reported effect sizes that are generally higher than d=0.5 (eg, chronic low back pain: d=0.77^1^; irritable bowel syndrome: d=0.79).^2^ However, in another OLP study for patients suffering from major depressive disorder,^5^ the authors reported an effect size of d=0.54 while stating that the study was limited by low statistical power (ie, the findings did not support the hypothesis that OLPs are effective in depression). Since PMS is not only characterised by physical complaints, yet also by psychological symptoms such as depressive mood, and since there is no specific research on OLP effects and effect sizes in PMS, we considered a conservative medium effect size as more appropriate. This resulted in a more conservative sample size.

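### The sample-size section equates f=0.25 with d=0.5 in a three-arm design, so its figure of 36 is not the number needed for a 0.5 SD effect and calling 150 conservative is unsupported

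*Protocol article*

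**What the plan says.** The Sample size section gives two sets of calculations.

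- **ANCOVA.** For "an analysis of covariance for three groups", it reports 206 participants at 90% power, against "a total sample size of 158 participants for a power of 0.8". The target is "to detect a medium effect size of f=0.25 (equals d=0.5) with an alpha-level of 0.05".
- **Repeated-measures ANOVA, three groups by three cycles.** "If the correlation for the outcome among the different time points (1–3 cycles) is assumed to be 0.5"; the interaction is then assessed with "a power of 0.8 and a medium effect size of f=0.25, the required samples size is 36 (12 per group". It adds 30 for the main effect of cycle and 108 for the main effect of group.

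It continues: "On this basis, we chose a conservative total sample size of 150 participants (50 per group". The choice is then defended by noting that published open-label placebo studies mostly reported d above 0.5 (0.77 and 0.79, with 0.54 in depression).

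Two other sections matter. Statistical analysis makes the group-by-cycle interaction the term of main interest, treats the arm means as equal at C1, and specifies an ordered linear contrast with OLP− between TAU and OLP+. Rationale states two hypotheses, both about adjacent arms: OLP+ against OLP−, and OLP− against TAU.

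**The concern.** Cohen's f is the standard deviation of the group means divided by the within-group SD. It equals d/2 only with two equal groups. The article applies that identity to three groups and carries the same f into an interaction, where f has another meaning again: the root mean square of the nine cell interaction terms, divided by the SD at one occasion. Because the arms start equal and differ only later, much of an arm difference is absorbed by the main effects. A given f then corresponds to a much larger difference between arms.

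This is the only power basis the article states. A reader told that 36 would do for a medium effect equal to d=0.5, and that 150 is conservative, could take a null result on the treatment rationale as strong evidence of no effect. The stated calculation does not justify that.

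**Working it through.** **Inputs.** From Sample size: alpha 0.05, f=0.25, three groups, m=3 cycles, correlation ρ=0.5, and N of 158, 206, 36, 30, 108 and 150. From Statistical analysis: equal C1 means, with OLP− between TAU and OLP+. Equal spacing of the arms and the time course of the effect are my assumptions, so I vary them.

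**Step 1: reproduce the stated figures** (noncentral F, G*Power default definitions).

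- ANCOVA: λ = f²N, numerator df 2. N=158 gives λ = 0.0625 × 158 = 9.875 and power 0.802. N=206 gives 0.901. N=150 gives λ = 9.375 and power 0.78.
- Interaction: λ = f²Nm/(1−ρ), df 4 and 2(N−3). N=36 gives λ = 0.0625 × 36 × 3/0.5 = 13.5 and power 0.823.
- Cycle: same λ formula, df 2 and 2(N−3). N=30 gives power 0.840.
- Group: λ = f²Nm/[1+(m−1)ρ], df 2 and N−3. N=108 gives λ = 0.0625 × 108 × 3/2 = 10.125 and power 0.809.

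Every stated N reproduces. The computation is right; the fault is in what f=0.25 is said to mean.

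**Step 2: f and d with three groups.** Let D be the difference between the highest and lowest arm means, in SD.

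- Equally spaced (0, D/2, D): f = D/√6. So f=0.25 is D = 0.25 × √6 = 0.61, and D=0.5 is f=0.204.
- Two arms equal (0, 0, D): f = D√2/3. So f=0.25 is D=0.53, and D=0.5 is f=0.236.

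**Step 3: f for the interaction.** Take improvements from C1 of TAU (0, 0, 0), OLP− (0, 0.25, 0.25) and OLP+ (0, 0.5, 0.5). After removing row and column means, the interaction terms are:

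- TAU: 0.167, −0.083, −0.083
- OLP−: 0, 0, 0
- OLP+: −0.167, 0.083, 0.083

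The sum of squares is 0.0833, so f = √(0.0833/9) = 0.096. An f of 0.25 therefore needs 0.5 × 0.25/0.0962 = 1.30 SD.

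| Pattern (arms equal at C1) | OLP+ vs TAU implied by f=0.25 | f at 0.5 SD | Power at 36, for 0.5 SD | Power at 150, for 0.5 SD |
|---|---|---|---|---|
| Equally spaced, sustained at C2 and C3 | 1.30 SD | 0.096 | 0.16 | 0.62 |
| Two arms equal, sustained | 1.125 SD | 0.111 | 0.21 | 0.76 |
| Equally spaced, linear ramp over cycles | 1.50 SD | 0.083 | 0.13 | 0.48 |

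These powers are for the 4-df omnibus interaction test, the one from which the 36 was derived.

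**Step 4: closer to the planned analysis** (illustration: equally spaced arms, sustained effect, ρ=0.5, N=150, 0.5 SD for OLP+ versus TAU).

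- Linear group contrast by cycle, without the baseline constraint: power about 0.73 (2 df), or 0.82 (1 df, C1 against later cycles).
- With the baseline constraint, using the C2/C3 average, no dropout and a normal approximation: the residual variance is (1+ρ)/2 − ρ² = 0.75 − 0.25 = 0.5, and SE = √(2 × 0.5/50) = 0.141. OLP+ versus TAU at 0.5 SD: 0.5/0.141 − 1.96 = 1.58, power about 0.94.
- An adjacent comparison, if each step is 0.25 SD: 0.25/0.141 − 1.96 = −0.19, power about 0.42. For ρ from 0.3 to 0.7 (residual variance 0.56 to 0.36) it is 0.39 to 0.55.

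**The case against.** The authors could fairly reply as follows.

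- *The equivalence with d=0.5 is written once, in the ANCOVA sentence.* True. Extending it to the repeated-measures figures is an inference. But the same medium f=0.25 is carried over, and the final choice is defended against published d values. That defence works only if f=0.25 means d=0.5.
- *For the ANCOVA the mislabelling is modest.* Agreed: 0.53 to 0.61 SD rather than 0.5. The weight lies in the interaction.
- *150 is conservative relative to 36, 30 and 108, which is the stated basis, and 158 and 206 are disclosed.* This stands in part. Falling 8 short of 158 costs about 2 points of power and would not matter alone. But 36 rests on the misread f, 30 concerns change over cycles and does not bear on differences between arms, and 108 is for a group effect averaged over all cycles, not the interaction of main interest.
- *The exact 1.30 SD depends on a pattern the protocol does not fix.* True, hence the range of 1.1 to 1.5 SD. No pattern tried comes near 0.5 SD.

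A reader might go further and infer that the trial is underpowered and needs more participants, for instance the 219 that the omnibus interaction test requires at 0.5 SD under the first pattern. The document does not support that. The omnibus test is not the planned one; the ordered contrast with equal baselines is more powerful (Step 4). Nor does the protocol say that d=0.5 spans TAU to OLP+ in two equal steps. If 0.5 SD were meant for each adjacent pair, the formula in Step 4 would give about 0.94 for each, so the 0.42 is conditional.

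**Conclusion.** The point holds as a misstatement of the power basis. The stated equivalence is wrong for three arms, and 36 is the number for an OLP+ versus TAU difference in change of about 1.1 to 1.5 SD, not 0.5 SD. At 0.5 SD, the omnibus test behind that figure has power of 0.13 to 0.21 at 36 and 0.48 to 0.76 at 150 across the patterns in the table. The description of 150 as conservative is therefore unsupported.

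These results assume equal C1 means, as the protocol does, together with its correlation of 0.5 and sphericity. Whether 150 is enough for the planned ordered contrast and for the two adjacent-arm hypotheses is not established either way, because the target difference between named arms is never stated. The illustrations suggest good power from end to end at 0.5 SD and weak power for steps of 0.25 SD.

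**What to change.** Keep 150 and restate its basis in the Sample size section:

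1. Delete the parenthesis equating f=0.25 with d=0.5, and stop calling the sample size conservative, both where 150 is chosen and in the section's closing sentence.
2. Drop 36 and 30 as justification.
3. State the target difference between named arms in SD, with the assumed spacing of the arms, the course over C2 and C3, and the correlation.
4. Report the power of 150 for the planned baseline-constrained linear contrast by cycle, and for each of the two adjacent-arm hypotheses in Rationale, with a range of correlations such as 0.3 to 0.7 and an allowance for dropout.

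The 0.94 and 0.42 above are illustrations for comparisons on the C2/C3 average, which Statistical analysis does not name. They should not be inserted as they stand; the authors should derive their own figures from the target they choose.

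The cost is a text change, with no effect on sample size, model or conduct. The downside is that the stated power for the adjacent comparisons is likely to look less favourable.

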### Statistical analysis

For the testing of the primary hypotheses, the daily data from three menstrual cycles of a symptom diary is examined. Because of the hierarchical structure of the data (menstrual cycles as level-1 are nested within participants as level-2) and given our aim to predict post-interventional changes between menstrual cycles as the primary outcome, a multilevel modelling approach will be adopted. Multilevel models take care of the interdependence of the hierarchical data that arises due to the fact that observations within the same individual are typically more similar to each other compared to observations between individuals.^30 31^ Here, we will analyse temporal changes across menstrual cycles of symptom intensity and interference among the different study groups. To compare a TAU group with two intervention groups and to evaluate the effect of the applied treatment rationale, the following linear a priori contrast will be tested for the factor study group: TAU<OLP−<OLP+. Thus, based on published findings,^6^ we expect that the effect of OLP− lies between that of TAU and OLP+. Out statistical model contains menstrual cycle as within-subject factor with three levels (C1, C2 and C3), study group as between-subject factor with three levels (TAU, OLP+ and OLP–), and the interaction between the two factors. In line with recommendations by Fitzmaurice *et al*,^32^ we will treat baseline values (ie, values at C1) as a part of the outcome vector and assume that the means among study groups are equal at baseline since participants are randomised. The model contains the two main effects study group contrast (defined above) and menstrual cycle (temporal effect) plus the interaction between the two. We will be primarily interested in the interaction term as it tests for the differential temporal change between study groups in order as defined in the linear contrast.

Analyses of secondary outcomes are based on the same multilevel model as used for primary outcomes, but will be considered exploratively, thereby not correcting for multiple tests.^33^

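### The requirement of 108 for the study-group main effect lets the pre-randomisation cycle C1 carry a group effect that the plan's own model sets to zero

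*Protocol article*

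**What the plan says.** The Sample size section first gives an analysis of covariance calculation (158 participants for power 0.8, 206 for power 0.9) "to detect a medium effect size of f=0.25 (equals d=0.5) with an alpha-level of 0.05". It then turns to a repeated-measures analysis of variance with three cycles and three groups, on this condition: "If the correlation for the outcome among the different time points (1–3 cycles) is assumed to be 0.5". With alpha 0.05, power 0.8 and f=0.25, it reports 36 for the group-by-cycle interaction and 30 for the cycle effect. For the third term it says: "for the main effect of study group we would need 108 participants (36 per group". The conclusion follows directly: "On this basis, we chose a conservative total sample size of 150 participants (50 per group".

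The Statistical analysis section makes C1 the baseline, keeps it in the outcome vector, and will "assume that the means among study groups are equal at baseline since participants are randomised". It names the group-by-cycle interaction, ordered by a linear contrast across the three arms, as the term of primary interest. The Trial treatment and study arms section and Table 1 place one full screening cycle before randomisation at t0, so C1 is untreated in every arm.

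**The concern.** A between-groups calculation with three repeated measurements treats f as the group difference in the mean of all three. That suits a design with three post-treatment measurements. This trial has one baseline cycle and two treated cycles, and its model sets the group difference in the first to zero. An effect confined to C2 and C3 shrinks by one third when it is averaged over C1 to C3.

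At stake is the stated basis for N. Of the three repeated-measures requirements (30, 36 and 108), 108 is the largest, so it decides how conservative 150 appears. The analysis of covariance figure for 80% power, 158, lies above 150, so the repeated-measures figures are what support going below it.

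**Working it through.** **Inputs.** From the Sample size section: alpha 0.05, f=0.25, correlation rho=0.5, k=3 groups, m=3 cycles, target power 0.8, and 150 participants in equal arms. From the Statistical analysis section: no group difference at C1. My assumptions: SD 1 in each cycle, the same correlation between any two cycles, and no dropout.

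**Step 1: reproduce 108.** Noncentral F with lambda = f²·N·m / (1+(m−1)·rho), on 2 and N−3 degrees of freedom.
- m=3, N=105: lambda = 0.0625×105×3/2 = 9.84, power 0.797.
- m=3, N=108: lambda = 0.0625×108×3/2 = 10.125, power 0.809. This is the smallest N in equal arms that reaches 0.8, so 108 is reproduced.
- m=3, N=150: lambda = 14.06, power 0.924.
- m=2 (treated cycles only), N=108: lambda = 0.0625×108×2/1.5 = 9.0, power 0.758. The requirement becomes 120.

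The companion figures (36, 30, 158 and 206) reproduce as well. So 108 is reached only with C1 counted as a cycle that carries the group effect.

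**Step 2: set the C1 effect to zero.** With f=0.25 in C2 and C3 and none in C1, the effect on the three-cycle mean is 0.25×2/3 = 0.167, and lambda is multiplied by 4/9.
- N=108: lambda = 10.125×4/9 = 4.5, power 0.449.
- N=150: lambda = 14.06×4/9 = 6.25, power 0.593.
- 80% power needs N=237.

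Simulation (4,000 runs per N; arm means −0.306, 0 and +0.306 SD in C2 and C3) gives 44.4% and 58.8%. Over rho from 0.3 to 0.8, power runs from 54% down to 36% at 108, and from 70% down to 48% at 150.

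**Step 3: the other reading of f.** If 0.25 is the effect on the three-cycle mean, the treated-cycle effect must be 0.25×3/2 = 0.375. With the plan's own conversion (f=0.25 equals d=0.5, so d=2f) that is d=0.75.

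**Step 4: analyses that use C1 as a baseline.** Effect f=0.25 in C2 and C3, rho=0.5.
- Mean of C2 and C3, no adjustment: variance (1+0.5)/2 = 0.75. At 150, lambda = 0.0625×150/0.75 = 12.5, power 0.890. Requirement 120.
- The same mean adjusted for C1, as an approximation to the planned equal-baseline model: residual variance 0.75−0.25 = 0.50. At 108, lambda = 13.5, power 0.911. At 150, lambda = 18.75, power 0.977. Requirement 81. Simulation gives 90% and 97%.

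**Step 5: the interaction, without the baseline constraint.** The profile 0, 1, 1 over the three cycles has variance 2/9, so lambda = (2/9)·f²·N·m/(1−rho). At 150 this is (2/9)×0.0625×150×3/0.5 = 12.5.
- Omnibus test, 4 degrees of freedom: power 0.813; 80% needs 147.
- Linear contrast by cycle, 2 degrees of freedom, evenly spaced arms: power about 89%.

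**The case against.** The strongest reply is that 108 is no slip in arithmetic. It is the right output of the routine described, and if f is the effect on the cycle-averaged mean, as that routine defines it, 108 does give 80% power. The article never says that f=0.25 refers to the treated cycles. This stands, and it makes the 45% and 59% conditional. It does not rescue the paragraph, because that reading implies d=0.75 in the treated cycles. The plan presents its medium effect as a cautious choice against earlier open-label placebo trials at d=0.77 and 0.79, and d=0.75 is almost the same size.

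The second reply is that the low powers belong to an unadjusted test that is not the planned analysis, and that the group main effect is not the term of primary interest. Both points stand. A reader might infer from 59% that the trial is underpowered at 150. The documents do not support that: the equal-baseline assumption that removes the effect from C1 also gives the planned model about 98% power at 150, and the interaction keeps 81% to 89% without it. A reader might also take the plan to promise 80% or more for the main effect at 150. It states power 0.8 at 108 and gives no power at 150; the 92% in the working is only what the same formula would yield.

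**Conclusion.** The requirement of 108 conflicts with the plan's own model and does not support 150 in the way the text suggests. Either the power is wrong (about 45% instead of 80% at 108, if f=0.25 applies to C2 and C3), or the effect assumed is not the cautious medium one claimed (f=0.375 in the treated cycles). The 45% rests on rho=0.5, equal variances, no dropout and the unadjusted three-cycle average.

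The fault is confined to the printed justification. The chosen 150 remains defensible on the planned analysis. The omnibus interaction is the narrowest case, since its 80% requirement of 147 assumes complete data.

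**What to change.** In the Sample size section:
- State that f=0.25 is the group effect in C2 and C3.
- Replace 108 with a requirement based on those two cycles: 120 unadjusted, or about 81 adjusted for C1, at correlation 0.5.
- Report the power at 150 for the planned contrast-by-cycle test under the equal-baseline model.
- Stop citing the group main effect averaged over C1 to C3 as a basis for N. It can stay in the model as a component of the interaction.

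The cost is one recalculation and a reworded paragraph. Neither N nor data collection changes.

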### Statistical analysis

For the testing of the primary hypotheses, the daily data from three menstrual cycles of a symptom diary is examined. Because of the hierarchical structure of the data (menstrual cycles as level-1 are nested within participants as level-2) and given our aim to predict post-interventional changes between menstrual cycles as the primary outcome, a multilevel modelling approach will be adopted. Multilevel models take care of the interdependence of the hierarchical data that arises due to the fact that observations within the same individual are typically more similar to each other compared to observations between individuals.^30 31^ Here, we will analyse temporal changes across menstrual cycles of symptom intensity and interference among the different study groups. To compare a TAU group with two intervention groups and to evaluate the effect of the applied treatment rationale, the following linear a priori contrast will be tested for the factor study group: TAU<OLP−<OLP+. Thus, based on published findings,^6^ we expect that the effect of OLP− lies between that of TAU and OLP+. Out statistical model contains menstrual cycle as within-subject factor with three levels (C1, C2 and C3), study group as between-subject factor with three levels (TAU, OLP+ and OLP–), and the interaction between the two factors. In line with recommendations by Fitzmaurice *et al*,^32^ we will treat baseline values (ie, values at C1) as a part of the outcome vector and assume that the means among study groups are equal at baseline since participants are randomised. The model contains the two main effects study group contrast (defined above) and menstrual cycle (temporal effect) plus the interaction between the two. We will be primarily interested in the interaction term as it tests for the differential temporal change between study groups in order as defined in the linear contrast.

Analyses of secondary outcomes are based on the same multilevel model as used for primary outcomes, but will be considered exploratively, thereby not correcting for multiple tests.^33^

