### Trial treatment and study arms

Following recruitment and verification of study eligibility - including a prospective PMS screening for one menstrual cycle - qualified women are allocated randomly by means of a random allocation sequence using the built-in random number generator in Microsoft Excel to one of the three study groups at the study visit (t0) and also are informed before any intervention, respectively the control contact starts: (1) a TAU group, (2) an OLP+ group and (3) an OLP− group (see also figure 2).

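### The primary model assumes equal group means at C1 but also lists a study-group main effect that leaves those means free, so two different primary analyses are described

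*Protocol article*

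**What the plan says.** All of the relevant text is in the Statistical analysis section of the protocol article.

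- Baseline handling: "we will treat baseline values (ie, values at C1) as a part of the outcome vector", and the plan will "assume that the means among study groups are equal at baseline since participants are randomised".
- Fixed effects, first statement: a three-level cycle factor that includes C1, with "study group as between-subject factor with three levels (TAU, OLP+ and OLP–), and the interaction between the two factors".
- Fixed effects, second statement, directly after the baseline assumption: "The model contains the two main effects study group contrast (defined above) and menstrual cycle (temporal effect) plus the interaction between the two".
- Term of primary interest: "We will be primarily interested in the interaction term as it tests for the differential temporal change between study groups". The groups are ordered by a linear contrast with TAU lowest, OLP− in the middle and OLP+ highest.

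C1 precedes randomisation. The section on trial treatment and study arms describes verification of eligibility "including a prospective PMS screening for one menstrual cycle - qualified women are allocated randomly" at the t0 visit. The equal-means assumption is therefore justified by design. Secondary outcomes use the same multilevel model.

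**The concern.** Once C1 is part of the outcome, equal baseline means are a restriction on the model: no group term may act at C1. A group main effect together with a group-by-cycle interaction over all three cycles gives each group, or each value of the contrast, its own C1 mean. The article states that fixed-effects list twice and nowhere drops or constrains the term. An analyst who follows the assumption and one who follows the list would fit different models to the same data.

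The difference falls on the primary test. The constrained model uses the estimated relation between C1 and later cycles to correct chance imbalance at C1. The listed model subtracts C1 in full, that is, with a fixed slope of 1. At stake are precision and an unambiguous primary model, for both primary outcomes and for every secondary outcome analysed in the same way.

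**Working it through.** **1. The plan's own figures.** The Sample size section gives 158 and 206 (analysis of covariance, power 0.8 and 0.9) and 36, 30 and 108 (repeated measures: interaction, cycle, group). Noncentral F calculations with f=0.25, alpha 0.05, three groups, three cycles and r=0.5 used these noncentralities:
- covariance analysis: f²N, with 2 and N−4 df;
- interaction and cycle: 3f²N/(1−r);
- group: 3f²N/(1+2r).

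All five figures reproduce exactly, so the sample-size arithmetic is not in question.

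**2. Inputs for the comparison.** From the Sample size section: r=0.5, 50 per group, d=0.5, two-sided alpha 0.05. Assumed here: complete data, the same SD (set to 1) at each cycle, the same correlation between all cycles, and contrast scores −1, 0, +1. The plan gives the order of the groups but not their spacing.

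**3. What the listed model implies at C1.** Let s be the contrast score. The mean at cycle t is μ_t + s(β + γ_t), with γ at C1 set to 0. The OLP+ minus TAU difference at C1 is 2β. Equal C1 means require β=0, but β is the listed main effect. Other full-rank codings move the C1 difference to other coefficients and still leave it free.

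**4. What the interaction then estimates.** With β free and complete data, it is the difference in mean change from C1. In one simulated data set with no true effect, the OLP+ minus TAU estimate at C3 was −0.0221 from the listed model, −0.0221 from raw change scores and 0.0587 from the constrained model. This shows the identity, and that the two models can differ in sign.

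**5. Precision.** Let V be the per-woman variance factor. Then SE(OLP+ − TAU) = √(2V/50), and power = Φ(0.5/SE − 1.96).

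Single post-baseline cycle:
- as listed: V = 2(1−r) = 1.00, SE 0.200, power 0.705;
- constrained: V = 1−r² = 0.75, SE 0.173, power 0.823;
- variance ratio 1.00/0.75 = 1.33. For 80% power, 63 versus 48 women per group.

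Average of C2 and C3:
- as listed: V = (1+r)/2 + 1 − 2r = 0.75, SE 0.173, power 0.823;
- constrained: V = (1+r)/2 − r² = 0.50, SE 0.141, power 0.942;
- variance ratio 0.75/0.50 = 1.50.

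Joint 2-df test of contrast by cycle, with true effects of 0.5 SD (OLP+) and 0.25 SD (OLP−) versus TAU at both cycles:
- as listed: the interaction coefficients have variance 0.0100 and covariance 0.0050, so noncentrality = 0.25² × 2/0.0150 = 8.33;
- constrained: variance 0.0075 and covariance 0.0025, so noncentrality = 0.25² × 2/0.0100 = 12.5;
- power with 2 and 294 df: 0.73 versus 0.89.

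**6. Sensitivity to the correlation (equal variances).** The single-cycle ratio is 2/(1+r): 1.54 at r=0.3, 1.33 at 0.5, 1.18 at 0.7. For the C2/C3 average it is 1.88, 1.50 and 1.25.

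**7. Sensitivity to the C1 variance.** Women are selected on C1 diary ratings, so the C1 spread may differ. Let k be the C1 SD divided by the later SD. The single-cycle ratio is (1 + k² − 2rk)/(1−r²). At r=0.5:
- k=1: 1.00/0.75 = 1.33;
- k=0.7: 0.79/0.75 = 1.05;
- k=0.5: 0.75/0.75 = 1.00.

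If selection cuts the C1 SD to 0.7 of its unselected value but the slope of later cycles on C1 stays 0.5, the later variance is 0.75 + 0.25 × 0.49 = 0.8725. The change variance is then 0.8725 + 0.49 − 2 × 0.5 × 0.49 = 0.8725, and the ratio is 0.8725/0.75 = 1.16. A k above 1 would increase the loss. The values of k are assumptions; the article gives none.

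**The case against.** The strongest reply is that the article states the constraint outright and names the model terms only in words, without an equation or coding, so the intended analysis may well be the constrained one. An equivalent constraint could also be written with a main effect present. This stands in part: the text does not establish which model will be run. It does not remove the contradiction, because both descriptions of the fixed effects include the term and neither mentions a constraint.

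A reader might go further in three ways that the article does not support.

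- That the listed analysis is biased or ignores baseline. It subtracts C1 in full, is unbiased under randomisation and has valid type I error. Only the fixed slope of 1 is inefficient.
- That the trial loses the equivalent of 50 of its 150 women. That figure (150/1.50 = 100) comes from a C2/C3 average, which the article does not define as an endpoint, and from equal variances, which selection on C1 makes doubtful. The single-cycle equivalent is 150/1.33, about 112.
- That the sample size depended on the constraint. The repeated-measures calculation already rests on a group-by-time model with a group main effect. The article justifies the constraint by a cited recommendation and by randomisation. Its remark about more precise estimation concerns multilevel modelling in general.

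**Conclusion.** The inconsistency is real and nothing elsewhere in the article resolves it. Its cost is efficiency and an ambiguous primary model, not validity. If the model is fitted as listed, the primary comparison generally has a larger variance than under the constraint the plan says it adopts. At the planning values, power for d=0.5 at a single cycle falls below 0.8, while power for the C2/C3 average stays above it. These figures rest on r=0.5, complete data and equal variances across cycles. Identity with the change-score analysis is exact only for complete data and approximate when cycles are missing. The penalty could be close to nil if selection markedly narrows the C1 spread. Should be fixed.

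**What to change.** Replace the sentence listing the model terms with one that imposes the stated assumption: one C1 mean common to all groups, cycle effects for C2 and C3, and the linear group contrast interacting with C2 and with C3 only, with no study-group main effect. State the contrast scores. Keep the pre-specified contrast-by-cycle interaction as the primary test, as one joint 2-df test of the C2 and C3 contrast terms for each primary outcome. Two separate tests per outcome would add multiplicity. Let the C1 variance differ from C2 and C3, for example with an unstructured 3×3 covariance, because women enter on the strength of their C1 ratings.

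The cost is a sentence or two in the Statistical analysis section, carried through to the secondary outcomes that use the same model. It needs no new data, no change in sample size and no burden on participants.
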